##### Tampa Scale of Kinesiophobia

This tool is an 11-item questionnaire based on a 7-point Likert scale (1=strongly disagree, 2=disagree, 3=agree, 4=strongly agree) that is used to evaluate fear of exercise injury in patients with chronic pain and will help us assess whether Tuina can reduce patients’ fear of movement and enhance their rehabilitation participation. It will also be applied at baseline and at 4-, 8-, and 16-week follow-up. Higher TSK-11 scores indicate a greater fear of pain, and a score above 24 is considered high-level kinesiophobia.

##### Functional Movement Screen

The FMS Figure 3A and B is a standardized field-expedient test cell designed to assess the quality of movement and has been used clinically in prescreening and in sports injury research. It will be used to assess objective physical function at baseline and 4-week follow-up. This tool uses 7 functional movements to assess movement pattern deficits and asymmetries, including deep squat, hurdle step, inline lunge, shoulder mobility, active straight leg raises, trunk stability pushup, and rotary stability. By assessing overall movement patterns, the FMS can comprehensively evaluate the impact of Tuina on patients’ motor function recovery. In this study, we will only evaluate the deep squat and hurdle step.

**Figure 3 figure3:**
[figure not shown]
Action demonstration: (A, B) FMS, (C) WBLT, and (D) TUG test. FMS: Functional Movement Screen; TUG: Timed Up and Go; WBLT: Weight Bearing Lunge Test.

##### Timed Up and Go

The TUG Figure 3D test is a simple and effective way to evaluate a patient’s ability to rise from a chair, walk, and turn, which is clinically applicable and reliable across multiple populations. Given that patients with KOA often experience walking difficulties and balance impairments, the TUG test offers a direct measure of functional mobility highly relevant to daily activities. By assessing TUG scores before and after our intervention, we can assess Tuina’s effects on mobility and balance, thereby verifying its clinical effectiveness. It will be used to assess objective physical function at baseline and 4-week follow-up.

At the beginning of the test, the patient will sit in a chair with their feet flat on the ground and their hands on their knees. We will ask them to get up, walk 3 m, turn around, and return to the chair. During this procedure, the evaluator will record the time it takes for the patient to complete the test. The longer the time, the higher the risk.

##### Weight Bearing Lunge Test

The WBLT Figure 3C is an ankle dorsiflexion activity under closed kinetic chain exercise of the knee joint, and its reliability and effectiveness have been widely recognized. It will also be applied at baseline and at 4-, 8-, and 16-week follow-up. Researchers have identified a potential relationship between the limited range of dorsiflexion motion in the ankle and knee kinematics, which may increase the risk of knee injury [29].

Before the test, a tape measure with a scale mark will be placed on the floor. During the test, the patient will be asked to face the wall, stand with one foot in front of the other, step on the tape on one side, and point the toes vertically toward the wall (initially at an appropriate distance from the wall), keeping the longitudinal axis of the foot in the center of the tape. They will keep the heel close to the ground and gradually move the knee forward. If the knee touches the wall, they will slowly move the knee and then the leg back and then repeat bending the knee toward the wall until the heel is about to leave the ground.

The assessor will measure the distance between the toes and the wall 3 times, calculate the average of the measurements, and record the results.

### Cointervention Assessments

Patients will be advised not to receive other KOA interventions (eg, acupuncture, intraarticular injection) during the study. Additional interventions will be meticulously recorded.

### Safety Assessments

We will also pay close attention to adverse events. Throughout the trial period, any adverse events or phenomena observed will be carefully recorded in the designated case report form (CRF). This documentation will include the precise timing of the event, the accompanying symptoms, the severity of the condition, its duration, the therapeutic measures implemented, and the outcome. The research team will carefully analyze the correlation between adverse events and the required intervention, recording their details, signs, and precise dates for future reference.

### Statistical Analysis

IBM SPSS Statistics 27.0 will be used for all data analyses. The different baseline characteristics of the 2 groups will be described. Data will be presented as the mean (SD) or the median (IQR) for continuous variables and as frequency distributions for categorical variables. The 2-sample *t* test for quantitative data or the chi-square test for qualitative data will be performed as a homogeneity test, and covariance analysis will be performed if an adjustment is needed for a baseline characteristic. Analysis will focus on whether statistically better treatment outcomes can be achieved in the intervention group. *P*<.05 is considered statistically significant and the tests are 2-sided. If data loss occurs, we will use multiple imputations to create several datasets to replace missing values and reduce bias. For repeated-measures data across 4 time points, we will apply linear mixed effects models to handle unequal intervals and account for individual random effects. In addition, repeated-measures ANOVA will test the statistical significance of variable differences between time points. Combining these methods will help reveal variable trends over time and provide reliable statistical support for the findings.

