### Participants

All participants will be recruited from among patients with KOA visiting Shuguang Hospital affiliated with the Shanghai University of Traditional Chinese Medicine. Patients will first be enrolled based on their basic information, medical history, X-ray results, and WOMAC (Western Ontario and McMaster Universities Osteoarthritis Index) scores. Patients who are willing to participate in this trial and demonstrate an understanding of the objectives and methods of the study by providing signed informed consent will then be randomly assigned to 2 groups: a conventional treatment (control) group and a Tuina+conventional treatment (intervention) group.

At baseline, some information will be collected in order to account for potential confounding variables, including basic information (name, sex, age, height, weight, telephone number, profession). We will calculate the patients’ BMI using their height and weight. Physical activity levels will be assessed and recorded using a 3-tier classification (light, moderate, and vigorous). Additionally, we will document the types of comorbidities and medication use, including type, dosage, and frequency. These variables will be included in multivariate analyses to adjust for their potential confounding effects on pain perception and functional outcomes.

All participants will be evaluated 4 times: at baseline and at 4-, 8-, and 16-week follow-up.

The inclusion criteria are as follows:

A diagnosis of KOA according to American College of Rheumatology criteria [17]Average pain score in WOMAC≥4An abnormal lower limb line on the lower limb length X-rayThe patient’s age is 20-65 years, male or female.No other treatment in the past 4 weeks that may interfere with the results of this study

In addition, patients with unilateral KOA will be included in the study.

The exclusion criteria are as follows:

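### Two different rules govern covariate adjustment, one tied to baseline homogeneity tests, and neither guarantees regression adjustment for baseline WOMAC

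*Protocol article*

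**What the plan says.** Three statements in the protocol article bear on this point.

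- **Statistical Analysis, conditional rule.** A two-sample t test "or the chi-square test for qualitative data will be performed as a homogeneity test", and the same sentence goes on: "covariance analysis will be performed if an adjustment is needed for a baseline characteristic". The section sets a two-sided 5% level for its tests. It gives no other criterion for when adjustment is needed and names no covariate.
- **Participants, unconditional rule.** Of the baseline data it says: "These variables will be included in multivariate analyses to adjust for their potential confounding effects on pain perception and functional outcomes". The list comprises basic information (sex, age, height, weight and profession among it), BMI derived from height and weight, a three-level activity rating, and comorbidities and medication: "we will document the types of comorbidities and medication use, including type, dosage, and frequency". Baseline WOMAC is not on the list.
- **Statistical Analysis, longitudinal model.** Linear mixed models are planned for outcomes measured at four time points. For WOMAC these are baseline and weeks 4, 8 and 16 (Outcome Measures). No covariates are named for the model, and nothing says that the baseline means are constrained to be equal.

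The Abstract defines the primary outcome as improvement in WOMAC from baseline to week 16.

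**The concern.** The two rules cannot both govern the same analysis. Pain and function are WOMAC subscales, so the unconditional rule in Participants reaches the primary outcome, as does the conditional rule in Statistical Analysis. Whoever writes the final model has to choose between them, possibly with the data in view.

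The conditional rule is also a poor way to choose covariates. Under proper randomisation, baseline differences arise by chance. A homogeneity test therefore does not show which variables predict the outcome, and that is what makes adjustment worthwhile. Baseline WOMAC, the same measure taken earlier and already collected, is an obvious candidate. It is missing from one rule and only conditional under the other.

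At stake are the precision of the primary comparison and whether its model can be shown to have been fixed in advance.

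**Working it through.** **Inputs.** From Sample Size Calculation: SD 44.7, difference 32.6, two-sided α 0.05, β 0.1, dropout 20%, 48 per group. The correlation ρ between baseline and week-16 WOMAC is not in the document; I assume 0.3, 0.5 and 0.7. I also assume equal SDs at baseline and week 16.

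**1. The plan's own figure.** n per group = 2 × [SD × (z₀.₉₇₅ + z₀.₉₀) / difference]² = 2 × [44.7 × (1.96 + 1.28) / 32.6]² = 39.47, as stated (39.51 with unrounded normal quantiles). Rounded up to 40, 40 × 1.2 = 48. The formula has no baseline term, so the sample size is not affected by this point. Completers per arm: 48 × 0.8 = 38.4, taken as 38.

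**2. How often the conditional rule would adjust.** If adjustment means P<.05 at baseline, baseline WOMAC is adjusted for in about 5% of properly randomised trials (simulated 4.9% to 5.1%) and left unadjusted in about 95%. Across k independent baseline tests, the chance of at least one significant result is 1 − 0.95^k: 0.30 for k = 7 and 0.40 for k = 10. Which covariates enter is then largely chance.

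**3. Precision.** Relative to a single score with variance SD², the variance factor is 2(1 − ρ) for a change score and 1 − ρ² for ANCOVA on baseline. With complete data and time as a category, a mixed model with free baseline means gives the change-score contrast at week 16. Power is from the two-sample t test with SD = 44.7 × √factor, difference 32.6 and 38 per arm.

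| ρ (assumed) | Change factor | ANCOVA factor | Change power | ANCOVA power |
|---|---|---|---|---|
| 0.3 | 1.40 | 0.91 | 0.76 | 0.91 |
| 0.5 | 1.00 | 0.75 | 0.88 | 0.95 |
| 0.7 | 0.60 | 0.51 | 0.98 | 0.99 |

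For 90% power, the change score needs 56, 40 and 24 per arm, and ANCOVA needs 36, 30 and 21.

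**4. Does testing first harm validity?** I used a simulation of 40,000 trials per setting with 38 per arm: test baseline WOMAC at 5%, use ANCOVA if significant, otherwise the change score. Type I error was 0.042, 0.043 and 0.046 for ρ 0.3, 0.5 and 0.7. With the week-16 score as the fallback it was 0.046, 0.044 and 0.036. Always using ANCOVA gave about 0.050. Power of the test-first rule with the change-score fallback was 0.77, 0.89 and 0.98, against 0.90, 0.95 and 0.99 for ANCOVA throughout.

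**The case against.** The best reply is that baseline WOMAC is used whatever the homogeneity test shows, through the change-from-baseline outcome and the mixed model. That stands. It rules out the claim that the baseline information is lost whenever the test is non-significant. It also makes the change score, not an unadjusted week-16 score, the fair comparator. What survives is that a contrast with free baseline means uses baseline less efficiently.

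A reader might infer that testing first makes the P value anti-conservative. The simulation does not support this: a single fixed test-then-adjust rule was mildly conservative. Nor does the article say literally that P<.05 triggers adjustment. That is the natural reading, because the homogeneity test is the only basis offered. If it is not what was meant, the criterion is undefined and the choice is left to judgement after the data are seen.

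The Participants statement could also describe supplementary analyses alongside the main comparison, which would remove the conflict. The article does not say so. A full covariate list can properly be left to an analysis plan, but these two instructions both stand in the text shown and need reconciling.

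Finally, ρ is assumed, and the article does not say whether 44.7 is the SD of a score or of a change. The ratio of the two variances, (1 − ρ²) / [2(1 − ρ)] = (1 + ρ)/2, does not depend on that: 0.65, 0.75 and 0.85. The power figures do depend on it.

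**Conclusion.** The point holds as a conflict between two adjustment rules, together with the lack of any guarantee of regression adjustment for baseline WOMAC. Against a change contrast with free baseline means, adjustment would cut the variance by 35%, 25% or 15% at ρ 0.3, 0.5 or 0.7. With 44.7 read as the SD of a single score, that is about 15, 7 or 1 points of power. At ρ 0.3 the change score falls well short of the planned 90%; at 0.7 the difference hardly matters. These sizes rest on assumed correlations, equal SDs and 38 completers per arm. The conflict in wording rests on none of these. The consequence is lost precision and a model open to choice after the data are seen; no inflation of type I error is shown. This should be corrected, but it does not invalidate the design.

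**What to change.** - Delete the baseline homogeneity tests and the conditional adjustment rule; describe baseline characteristics without P values.
- Fix the primary analysis as a mixed model with WOMAC at weeks 4, 8 and 16 as responses and baseline WOMAC as a covariate in every case. Alternatively, keep baseline as a response and constrain the two group means to be equal there. Choose one form, so that baseline does not enter twice. Name the week-16 group contrast as primary.
- Reconcile the Participants section: either limit its variables to a short prespecified set in the primary model or move them to a sensitivity analysis. With at most 96 participants, the whole list (several levels each for profession, comorbidity and medication) is too long for the primary model.
- Adjust each secondary outcome for its own baseline value.

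The cost is small. WOMAC and the secondary measures are already taken at baseline, so no new data are needed. The article says that formal analysis had not started. Because recruitment was under way and Quality Assurance says that the protocol will not change during the study, the new wording should be dated and documented, as an amendment or in the analysis plan, before analysis begins.

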### Ethical Considerations

This protocol was approved in March 2025 by the Medical Ethics Committee of Shuguang Hospital affiliated with the Shanghai University of Traditional Chinese Medicine (approval number 2024-1560-143-01). All participants will provide signed informed consent, and upon completion of the study, they will receive a subsidy of 100 yuan (~US $14). Patient consent for publication is not applicable.

Data management is extremely important. In this study, electronic data will be stored on a dedicated computer in our research center. This computer will be protected by a password, a firewall, and an intrusion detection system, which can effectively prevent unauthorized access and data breaches, ensuring data security. In addition, data will be regularly backed up according to a set schedule to prevent loss. They will also be stored using a unified file-naming convention and directory structure for easy retrieval and management. Paper-based data, including CRFs, will be stored in locked filing cabinets at our research center. They will be organized and clearly labeled, and modifications will be recorded with the original content retained. Only authorized personnel will have access. Any personal information will be anonymized. Data will be retained as required by regulations to ensure integrity, traceability, and confidentiality.

Data access will be strictly controlled based on research roles and responsibilities. Principal researchers will have unrestricted access to perform their duties effectively. Other research team members will be granted access solely to the data essential for their specific tasks. Additionally, the Ethics Committee and regulatory authorities will have the right to review the data in accordance with relevant laws and ethical guidelines to ensure compliance with research standards. Additionally, all data access activities will be logged and subject to periodic review.

After the study, data will be properly stored following institutional and regulatory requirements. After the retention period, all data and records will be uniformly destroyed to ensure the long-term maintenance of participant privacy.

### Quality Assurance

The project manager will be exclusively responsible for conducting all quality assurance. Before the study, all researchers are expected to undertake a comprehensive and uniform protocol-specific training program, encompassing the study protocol, CRF filling, data collection, data entry, and standard of functional tests. During the study, the project manager will conduct periodic inspections on all study components to ensure rigorous adherence to the study protocol and accurate documentation of the research data. Functional tests will be evaluated by specific researchers. The protocol will remain unaltered during the study period.

## Results

We have successfully recruited 55 participants for the study, including those undergoing the intervention, those in follow-up, and those who have completed the study, with recruitment expected to be completed by September 2025. Data analysis has not yet been initiated. Upon completion of the study, the results will be submitted to a peer-reviewed journal for rigorous evaluation.

## Discussion

### Summary

The knee joint serves as a significant component of lower limb movements and acts as a pivotal link in the lower limb kinematic chain [30]. In the framework of kinematic chain theory [31,32], the lower limb is considered a harmonious and integrated unit, wherein the cooperative interplay of hip, knee, and ankle articulations is postulated as the vital factor for ensuring postural equilibrium and optimal gait function in the human body. The 3 joints are closely related, and any aberration in any of the links may culminate in the derangement of the lower limb’s force line and the diminution of joint stability, potentially leading to irregular muscle contraction patterns, abnormal joint stress, and irregular neuromuscular interaction. This condition eventually leads to incongruous patterns of lower limb movement. Therefore, in the treatment of KOA, a holistic approach should be implemented, focusing on the integrity and functionality of the entire musculoskeletal system rather than relying excessively on local interventions.

Holism is a fundamental characteristic of TCM. The application of holistic concepts and differentiation of syndromes in diagnostic and therapeutic processes is a central concern in clinical practice. The inclusion of Tuina therapy in KOA management represents a frequently used and effective treatment strategy. Moreover, Tuina can effectively complement the treatment regimen for the hip, knee, and ankle joints. Therefore, we will develop a comprehensive clinical trial to evaluate the efficacy of Tuina therapy based on hip-knee-ankle synergy in the treatment of KOA.

### Strengths and Limitations

To the best of our knowledge, this study is the first RCT to explore the clinical efficacy of Tuina therapy based on hip-knee-ankle synergy in patients with KOA. Our study will adopt a comprehensive approach to functional assessment, integrating both objective measurements and subjective patient-reported outcomes. This dual methodology will allow us to not only quantify improvements through standardized evaluation protocols but also capture patients’ personal experiences and perceptions of their recovery. By combining these perspectives, we seek to offer a more nuanced and complete assessment of how intervention affects physical function. The primary outcome measure used in this study is WOMAC, a validated and reliable tool specifically designed to assess the presence and severity of lower extremity pain, stiffness, and functional limitations associated with OA [33]. Numerous previous studies have used WOMAC in behavioral intervention trials for osteoarthritis, validating its use as an appropriate indicator of clinical efficacy in this context. Key Symptoms and Signs/TCM Syndrome Classification Quantitative Evaluation of KOA can assess the degree of pain, swelling, and accompanying symptoms. TSK-11 can accurately predict the degree of physical disability in this patient population [34]. The TUG test represents abilities related to ambulatory transitions, leg strength, and balance [35], the FMS is crucial in assessing the quality of movement, and the WBLT is used to assess ankle dorsiflexion activity.

We anticipate that the results of this study will demonstrate the effectiveness of Tuina therapy based on hip-knee-ankle synergy in improving pain relief, functional outcomes, and overall quality of life for patients with KOA. For example, we expect to observe statistically significant improvements in WOMAC scores, indicating reduced pain, stiffness, and functional limitations. We also expect to observe statistically significant improvements in TSK-11 scores, indicating reduced fear of movement in patients. Additionally, we expect to observe statistically significant improvements in TUG, FMS, and WBLT outcomes. Such improvements would suggest potential enhancements in patients’ physical activity and balance abilities. These potential findings would provide strong evidence supporting the integration of Tuina therapy into conventional treatment approaches for KOA, emphasizing the importance of considering the entire musculoskeletal system rather than focusing solely on localized treatments.

Although the study design inherently creates a potential imbalance in treatment dosage between the 2 groups, which may lead to differences in compliance and potentially affect the comparability of the results, several measures have been implemented to minimize the bias introduced by this imbalance. The assessor will be blinded to participants’ group allocations and remain unaware of the intervention methods used for the 2 groups. Additionally, information about the existence of another intervention group will not be disclosed to the patients, and they will be strictly instructed not to disclose any information related to their intervention to the assessor.

Our study was conducted in a single medical institution, a large tertiary hospital with 2 campuses in different regions of Shanghai that serve diverse patient populations. Although this setup partially mitigates the limitations of a single-center study, it does not fully replicate the diversity of multisite studies conducted across varied geographical areas. Future research should investigate the intervention’s effectiveness in multiple health care settings and populations to better understand its generalizability and real-world applicability.

